#### Land-based intervention

The land-based exercise intervention group will train in the exercise training facilities of the local association of fibromyalgia, or in the closer exercise centre. Cardiovascular exercises will incorporate walking at different speeds and continuous and rhythmic activities that affects large muscle groups and aerobic dance. Resistance strength training will include 1-3 set of 8-12 repetitions. The strengthening exercises will include biceps curls, arm extensions, arm side lifts, shoulder elevations, lateral leg elevations, stands up from seated position, lunge, sideways lunge and step-up/step-down. The load will be gradually increased as the strength of each person improves. We will use body weight at the start of the program and barbells (0.5-2 kg per exercise). Flexibility will be developed by static stretching at the end of the warm-up and cool-down periods.

#### Water-based intervention

The water-based exercise intervention group will train in a chest-high warm (~30°C) pool. A modified version of the land-based intervention, adapted to the restrictions and peculiarities imposed by water, will be used. The training intensity and the muscle groups activated will be as similar as possible in the two groups.

The cardiovascular exercises will include bicycling simulation (with the floater between legs), walking around the pool, continuous and rhythmic activities that affects large muscle groups and aerobic dance. The strength exercises will be performed at slow pace using water and aquatic materials as resistance. Flexibility exercises will consist of static stretching at the end of the warm-up and cool-down, as in the land-based intervention.

#### Usual care group (control)

Participants randomly assigned to the usual care (control) group will receive general advices from the exercise monitor about the positive effects of physical activity. We will prepare informative pamphlets describing the benefits of physical activity and general guidelines about how to increase the daily physical activity levels.

### Participant retention and adherence

To maximize adherence, several strategies will be implemented including music in all sessions, individualized attention at the intervention sessions, telephone calls following missed sessions, and the control of patients' pain rate before and after each session. Make-up sessions will be allowed in case of missing sessions (due to illness or any other reason).

### Primary outcomes measures

*Fibromyalgia Impact Questionnaire *(FIQ) is a self-administered questionnaire, comprising 10 subscales of disabilities and symptoms (physical function, work missed day, job ability, feel good, pain, fatigue, sleep, stiffness, anxiety and depression) and has been validated for Spanish fibromyalgia patients [30]. The total scores range from 0 to 100, with a higher score indicating greater effect of the condition on the person's life.

### Secondary outcomes measures

#### Tenderness and pain related measures

We will assess 18 *tender points *according to the American College of Rheumatology criteria for classification of fibromyalgia using a standard pressure algometer (FPK 20; Effegi, Alfonsine, Italy). The *tender point count*, total count of positive tender points, will be recorded for each participant. The *algometer score *will be calculated as the sum of the minimum pain-pressure values obtained for each tender point.

*The Visual analogic scale for pain *is a simple assessment tool consisting of a 10 cm line with 0 on one end, representing no pain, and 10 on the other, representing the worst pain ever experienced, which a patient marks to indicate the severity of her pain in the present moment. This scale will also be administered before and after each session during the intervention, to assess the acute effect of exercise on pain.

*The Pain Catastrophizing Scale *[37,38] will be used to assess three factors: rumination, magnification and helplessness associated to pain. It includes 13 items measured on a 5-point Likert scale ranging from 0 (not at all) to 4 (all the time). Higher scores indicate a greater tendency to catastrophize pain symptoms.

*The Chronic Pain Self-Efficacy Scale *[39,40], is a scale that measures efficacy expectations for coping with pain. It contains 22 items grouped into 3 subscales: self efficacy for pain management, self efficacy for coping with symptoms, and self efficacy for physical function. The scores are obtained by means of a Likert scale with a range of 0-10, where higher scores indicate better self efficacy.

#### Body composition

Weight and height will be measured, body mass index [weight (kg)/height(m^2^)] will be calculated, and skeletal muscle mass, total body water and fat free mass will be estimated with bioelectrical impedance analysis (InBody R20; Biospace, Gateshead, UK).

#### Functional capacity

Participants' functional capacity will be assessed by field-based fitness tests following the standardised Functional Senior Fitness Test Battery [41]. This battery assesses muscular strength, flexibility, balance and aerobic capacity by means of the following tests:

##### Lower body muscular strength

The "30-s chair stand test" involves counting the number of times within 30 s that an individual can rise to a full stand from a seated position with back straight and feet flat on the floor, without pushing off with the arms. The patients will perform one trial after familiarization [41].

##### Upper body muscular strength

The "Arm curl test" involves determining a number of times a hand weight (2.3 kg for women) can be curled through a full range of motion in 30 s [41]. Additionally, handgrip strength will be measured using a digital dynamometer (TKK 5101 Grip-D; Takey, Tokyo, Japan) as described elsewhere [42]. Patients will perform (alternately with both hands) the test twice allowing a 1-min rest period between measures. The best value of 2 trials for each hand will be chosen and the average of both hands will be used in the analyses.

##### Lower body flexibility

In the "chair sit and reach test", the patient seated with one leg extended, slowly bends forward sliding the hands down the extended leg in an attempt to touch (or pass) the toes. The number of centimeters short of reaching the toe (minus score) or reaching beyond it (plus score) will be recorded [41]. Two trials with each leg will be measured and the best value of each leg will be registered, and the average of both legs will be used in the analyses.

##### Upper body flexibility

The "back scratch test", a measure of overall shoulder range of motion, involves measuring the distance between (or overlap of) the middle fingers behind the back with a ruler [41]. Participants will perform this test twice, alternately with both hands, and the best value will be registered. The average of both hands will be used in the analyses.

##### Motor agility/dynamic balance

The "8 ft up and go test" involves standing up from a chair, walking 8 ft to and around a cone, and returning to the chair in the shortest possible time [41]. The best time of two trials will be recorded and used in the analyses.

##### Cardiorespiratory fitness

We will use the "6-min walk test". This test involves determining the maximum distance (meters) that can be walked in 6 min along a 45.7 m rectangular course [41,43].

*The International Fitness Scale *[44] is composed of five Likert-scale questions asking about the perceived patients' overall fitness, cardio-respiratory fitness, muscular fitness, speed-agility and flexibility in comparison with their friends' physical fitness ("very poor", "poor", "average", "good" and "very good").

#### Physical activity and sedentary behaviour

Physical activity and sedentary behaviour will be objectively (i.e. accelerometry) and subjectively (i.e. questionnaires) assessed:

##### Accelerometry

Women will be asked to wear an tri-axial accelerometer (ActiGraph GT3X+, Pensacola, Florida, US) for 8 consecutive days, starting the same day they receive the monitor, and will returned the accelerometers to the researcher 9 days later. Participants will be instructed to wear the accelerometer on their lower back attached by an elastic belt during waking as well as sleeping hours. For security reasons, participants will be asked to take them off while bathing.

We will exclude from the analyses bouts of 60 continuous minutes of 0 activity intensity counts, considering these periods as non-wearing time. Monitor wearing time will be calculated by subtracting the non-wear time and the sleeping time (recorded through a diary) from the total registered time for the entire day (typically 1,440 min). A recording of more than 20,000 counts per minute will be considered as a potential malfunction of the accelerometer and the value will be excluded from the analyses. The first day of recording will not be included in the analysis. A total of 7 days of recording with a minimum of ten or more hours of registration per day will be necessary to be included in the study. Physical activity levels will be shown as follows: (i) average physical activity, expressed as mean counts per minute. It is a measure of overall physical activity. We will calculate mean counts per minute by dividing the sum of total counts per epoch for a valid day by the number of minutes of wear time in that day across all valid days. We will also calculate the time engaged in light, lifestyle, moderate, and moderate and vigorous intensity physical activity based upon a standardized cut-off of 100-759, 760-1,951, 1,952-5,724, and at least 1,952 counts per minute, respectively. Sedentary time will be calculated as the amount of time accumulated below 100 counts per minute during periods of wear time.

*The Leisure time physical activity instrument *[45,46] is composed of 4 items with 3 activity levels: light, moderate, and vigorous (a short description of each category will be presented). Patients will be asked to recall the average number of hours a week during the previous 4 weeks that they had spent engaged in a particular type of physical activity and at what activity level. The scale will be simplified into the following 3 levels: (1) 0.5-1.5 h a week, (2) 2-4 h a week, and (3) more than 4 h a week, and the patient will be asked to provide answers in hours. The number of hours indicated by the patient for each intensity category will be summed to obtain the leisure time physical activity level for 1 week.

*The Physical activity at homework or workplace instrument *[45,46] is composed of 7 items with 3 categories for work performed at home (light, moderate and heavy activity) and 4 categories for employment (sedentary, light, moderate and heavy activity).The hours for each category will be summed to obtain the total score.

*The Sedentary Behavior Questionnaire *[47] consisted of reports of time spent in 9 sedentary behaviors (watching television, sitting while playing computer/video games, sitting while listening to music, sitting and talking on the phone, doing paperwork or office work, sitting and reading, playing a musical instrument, doing arts and crafts, sitting and driving/riding in a car, bus, or train).

The short version of the *ALPHA Environmental questionnaire *[48,49] will be used to assess the environmental perceptions physical activity. The questionnaire will provide information about types of residences in the neighborhood, distances to local facilities, walking or cycle infrastructure in the neighborhood, cycling and walking network, neighborhood safety, home and work/study environment mode of active travel.

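### The accelerometer rules leave no spare valid day, tie failure to inclusion in the study, and do not settle how night-time zero counts and sleep enter wear time and counts per minute

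*Protocol article*

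**What the plan says.** All the rules stand in the Accelerometry section of the protocol article.

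- **Days.** Women wear the monitor "for 8 consecutive days, starting the same day they receive the monitor". Then: "The first day of recording will not be included in the analysis".
- **Validity.** "A total of 7 days of recording with a minimum of ten or more hours of registration per day will be necessary". The sentence makes this a condition of inclusion in the study, not of inclusion in the accelerometer analysis.
- **When worn.** The belt is worn "during waking as well as sleeping hours" and comes off for bathing.
- **Non-wear.** The analysis excludes "bouts of 60 continuous minutes of 0 activity intensity counts, considering these periods as non-wearing time". The rule is not limited to waking hours.
- **Wear time.** "Monitor wearing time will be calculated by subtracting the non-wear time and the sleeping time (recorded through a diary) from the total registered time", which is given as typically 1,440 minutes per day.
- **Mean counts per minute.** The numerator is the total of a valid day's counts, the denominator is that day's wear minutes, and the result is taken over every valid day.

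Elsewhere, Objectives lists physical activity and sedentary behaviour among the secondary outcomes. Table 2 schedules accelerometry at baseline, post-intervention and detraining. Statistical analysis commits to intention-to-treat, multiple imputation for data missing through drop-out or non-compliance, and a sensitivity analysis for missing responses.

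**The concern.** Two things stand out.

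First, the number of valid days required equals the number available. A woman with six good days and one short day fails, and her six observed days go unused. The stated consequence is also worse than losing one outcome, because it is exclusion from the study. At baseline that would act as an eligibility criterion missing from Table 1. After randomisation it would be an exclusion based on behaviour that may differ by arm, which the intention-to-treat commitment rules out.

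Second, the monitor records the nights. A run of 60 or more zero-count minutes during sleep fits both quantities that are subtracted from registered time, and nothing says that such minutes are removed only once. The denominator of mean counts per minute leaves out sleep, yet the numerator is described as the day's total counts. Either feature makes the mean depend partly on how a woman sleeps. Sleep quality is itself a secondary outcome, so it cannot be taken for granted that the error is equal between arms.

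**Working it through.** **1. Valid days (reproduces the plan's own figure).** Days worn 8, first day dropped 1, usable days 8 − 1 = 7. Days required: 7. There is no spare day.

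**2. Share of women meeting the rule at one assessment.** The documents give no daily compliance figure. Assume that each day is valid with probability p, independently. Then P(7 of 7) = p^7, and P(at least 4 of 7) is the binomial upper tail.

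| Assumed p | 7 of 7 | Of 180 women at baseline | At least 4 of 7 |
|---|---|---|---|
| 0.99 | 93.2% | 168 | over 99.9% |
| 0.98 | 86.8% | 156 | over 99.9% |
| 0.95 | 69.8% | 126 | over 99.9% |
| 0.90 | 47.8% | 86 | 99.7% |

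If short days cluster in the same women, the loss at a given p is smaller than shown.

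**3. Wear time.** Let S be diary sleep, N waking non-wear, and O the minutes of zero bouts (60 minutes or longer) that fall within diary sleep. S, N and O are all assumptions.

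- Overlap removed once: W1 = 1,440 − S − N.
- Formula taken literally, with both terms subtracted in full: W2 = 1,440 − (N + O) − S = W1 − O.
- Inflation of mean counts per minute, numerator unchanged: W1/W2 − 1. Zero bouts add nothing to the numerator, so only the denominator moves.

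| S | N | O | W1 | W2 | Inflation |
|---|---|---|---|---|---|
| 480 | 0 | 60 | 960 | 900 | 6.7% |
| 480 | 0 | 240 | 960 | 720 | 33.3% |
| 480 | 30 | 60 | 930 | 870 | 6.9% |
| 480 | 30 | 240 | 930 | 690 | 34.8% |
| 480 | 30 | 360 | 930 | 570 | 63.2% |

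For sleep of 7 to 9 hours and waking non-wear of 30 to 60 minutes, the ranges are 6.5-7.7% at O = 60, 32.0-40.0% at O = 240 and 57.1-75.0% at O = 360. At O = 0 the two formulas agree.

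**4. Ten-hour limit.** If the 10 hours (600 minutes) are judged on W2, a day with S = 480 and N = 30 fails once 930 − O < 600, that is, once O exceeds 330. If they are judged on registered time, the overlap has no bearing on validity.

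**5. Numerator.** If counts during sleep equal a fraction f of waking counts and are left in, the mean rises by the factor 1 + f, on top of any effect from step 3. The documents give nothing from which to estimate f.

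**6. Activity bands.** A minute in a zero bout has no counts, so it cannot fall in a band that starts at 100 counts per minute or higher. On a valid day, the overlap leaves minutes in the light, lifestyle, moderate and moderate-to-vigorous bands unchanged.

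**The case against.** The strongest reply is that double subtraction is an inference. The section first excludes zero bouts and then defines wear time as what remains after non-wear and sleep. An analyst could fairly read this as the minutes that are neither, or could apply the bout rule to waking hours only. This stands: the text does not direct anyone to subtract twice, and the defect is that it leaves the overlap open. Processing order might be left to a fuller document. Here, however, the article states the formula itself, and that formula admits the wrong reading.

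The 10-hour criterion is worded in terms of registration, and the section uses registered time for the full 1,440 minutes. A reader might infer that the overlap makes days fail the limit. That follows only if the limit is applied to the reduced wear time, which the text does not say.

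A reader might also infer that the rule will discard many women. The documents do not support this. They report no compliance rate, the belt stays on day and night except for bathing, and at p = 0.99 only about 7% fail per assessment. Women who fail may be imputed as non-compliant. Multiplying over three assessments (for example 0.95^21 = 0.34) describes a complete-case analysis that the protocol does not plan. Imputation is only a partial answer, though: it would replace up to six valid observed days, and the reference to inclusion in the study leaves it unclear whether these women are imputed or removed.

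Finally, requiring a full week is coherent because it covers weekdays and weekend equally. That is a real advantage, and a reason to keep 7 of 7 as a sensitivity analysis.

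**Conclusion.** The point holds in limited form. It is certain from the text that all 7 usable days must be valid, that failure is tied to inclusion in the study, that zero bouts are not restricted to waking time, and that the numerator is described as the whole day's counts over a denominator without sleep. The literal exclusion contradicts intention-to-treat for randomised women.

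The size is not known. The share failing one assessment runs from about 7% to 52% over assumed daily validity of 0.99 to 0.90, under independence. The upward error in mean counts per minute arises only if the overlap is subtracted twice or sleep counts are kept, and its size depends on assumed night-time zero bouts. Any bias between arms would further require these to differ by arm, which is possible but not shown. The effect falls mainly on mean counts per minute, within the secondary accelerometry outcomes. The primary outcome (FIQ) and its sample-size calculation are affected only if the study-wide exclusion were actually enforced.

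**What to change.** Change the wording of the Accelerometry section before data are processed:

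1. Remove diary sleep first, then apply the 60-minute zero-count rule to waking time only.
2. Compute counts, minutes and the 10-hour criterion from that same waking wear time.
3. Accept a lower minimum of valid days for the accelerometer analysis, for example at least 4 of 7, with 7 of 7 as a sensitivity analysis.
4. State that failing the minimum affects inclusion in the accelerometer analysis, not in the study, and that these women's accelerometer outcomes are handled by the missing-data methods in Statistical analysis.

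The cost is wording and processing code, with no extra visits, participants or measurements. The downside is that averages from fewer days are somewhat noisier and may cover weekdays and weekends unevenly. The sensitivity analysis would show whether that matters.

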### Objectives

The primary objective of the *al-Andalus *physical activity randomised controlled trial (RCT) is to investigate the effectiveness of two types of exercise interventions (water- and land-based aerobic-strength training vs. a control group) on the overall impact of fibromyalgia (primary outcome), and on tenderness and pain-related measures, body composition, functional capacity, physical activity and sedentary behaviour, fatigue, sleep quality, health-related quality of life and cognitive function (secondary outcomes) in women aged 35-65 years with fibromyalgia. The intervention groups will train 3 days/week (60 min per session) for a 24-week period. We will also study the effect of a detraining period (i.e., 12 weeks with no exercise intervention) on the studied variables.

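### As written, the home-and-work physical activity total counts sedentary employment hours as activity, at odds with how the rest of the section treats sitting

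*Protocol article*

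**What the plan says.** The Objectives list physical activity and sedentary behaviour among the secondary domains: "functional capacity, physical activity and sedentary behaviour, fatigue, sleep quality, health-related quality of life and cognitive function (secondary outcomes"). The instruments are described under Secondary outcomes measures, Physical activity and sedentary behaviour.

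- **Home-and-work instrument, housework part.** It "is composed of 7 items with 3 categories for work performed at home (light, moderate and heavy activity").
- **Home-and-work instrument, paid-work part.** The remaining items are "4 categories for employment (sedentary, light, moderate and heavy activity").
- **Home-and-work instrument, score.** "The hours for each category will be summed to obtain the total score". No category is excluded and no weight is given.
- **Leisure-time instrument.** It carries the same citations and "is composed of 4 items with 3 activity levels: light, moderate, and vigorous". Its score is also a plain sum, over a period of one week: "The number of hours indicated by the patient for each intensity category will be summed to obtain the leisure time physical activity level for 1". It has no sedentary level.
- **Accelerometry.** "Sedentary time will be calculated as the amount of time accumulated below 100 counts per minute during periods of wear time". Light activity starts at 100 counts per minute, so the two do not overlap.
- **Sedentary Behavior Questionnaire.** Its nine behaviours include "doing paperwork or office work".

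**The concern.** The section uses two constructs, activity and sedentary behaviour, and three of its instruments keep them apart. The home-and-work total does not. An hour of office work counts as sedentary behaviour in one questionnaire and adds to a physical activity score in another.

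Two changes that matter in an exercise trial would then be misread. A woman who replaces sitting at work with light activity has become more active, but her total stays the same. A woman whose desk hours rise or fall gets a different total with no change in activity. The primary questionnaire has items on missed work and ability to do the job (Primary outcomes measures), so changes in working hours during the trial are conceivable. A group difference on this score could therefore be read as an activity effect when it reflects paid desk hours, or a real activity effect could be hidden.

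**Working it through.** **1. Is the sedentary category inside the sum?** The article states 7 items. Home categories 3 + employment categories 4 = 7, which reproduces the stated count. Sedentary employment is therefore one of the seven categories that the scoring sentence adds up.

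**2. What the score is.** Let A be light + moderate + heavy hours (home plus employment) and S be sedentary employment hours. As written, T = A + S. A sum restricted to active categories would be A.

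**3. Apply both rules to example profiles.** The weekly hours are assumed; the article gives none. Unless stated otherwise, each woman does 10 h light + 5 h moderate housework = 15 h.

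| Profile | T as written | A only |
|---|---|---|
| 35 h sedentary job | 15 + 35 = 50 | 15 |
| 35 h heavy job | 15 + 35 = 50 | 50 |
| Sedentary job, 10 h moved to light work | 15 + 25 + 10 = 50 | 15 + 10 = 25 |
| Sedentary job cut to 20 h | 15 + 20 = 35 | 15 |
| No job | 15 | 15 |
| No job, 30 h housework | 30 | 30 |

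- Rows 1 and 3: 10 more active hours leave T at 50.
- Rows 1 and 4: 15 fewer desk hours lower T from 50 to 35 with activity unchanged.
- Rows 2, 5 and 6: without sedentary employment, T = A.

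**4. Effect on a group comparison.** Because T = A + S, the group difference in mean change in T is the difference in change in A plus the difference in change in S. The second term is zero if desk hours change equally in the groups.

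**5. Effect on precision.** Assume A has SD 8 (variance 64), a share p of women holds a sedentary job of h hours, and S is independent of A. Then Var(S) = p(1 − p)h².

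- p = 0.2, h = 20: Var(S) = 0.2 × 0.8 × 400 = 64, so Var(T) = 128, twice 64.
- p = 0.3, h = 30: Var(S) = 0.3 × 0.7 × 900 = 189, so Var(T) = 253, about 4 times 64.

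Those are variances at one visit. The Statistical analysis section specifies ANCOVA with the baseline level of each outcome as a covariate, so the relevant quantity is the residual variance, Var(T) − Cov²/Var(T), where Cov is the covariance between visits. Assume S does not change and A correlates r between visits, so that Cov = 64r + Var(S).

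- r = 0.7, A only: 64 × (1 − 0.49) = 32.6.
- r = 0.7, first case: 128 − 108.8²/128 = 35.5, or +9%.
- r = 0.7, second case: 253 − 233.8²/253 = 36.9, or +13%.
- r = 0.5, A only: 64 × (1 − 0.25) = 48.
- r = 0.5, first case: 128 − 96²/128 = 56, or +17%.
- r = 0.5, second case: 253 − 221²/253 = 59.9, or +25%.

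With stable jobs, the loss of precision is modest. Changes in desk hours during the trial would add to it.

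**The case against.** **It is a published instrument, described in a condensed article.** The cited scoring is not shown, so one cannot tell whether the published total includes the sedentary item or whether category hours are also reported. This limits confidence about what will be done. It does not remove the point, because the article does not leave the scoring open. It states a rule, and that rule includes sedentary hours.

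**Equal scores for light and heavy work are normal for an hour count.** This is right. The leisure score is also unweighted, and lack of intensity weighting is not the fault here. The fault is that a category which the protocol itself calls sedentary is added to an activity total.

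**The rest of the domain covers the gap.** This stands as to importance. Activity and sedentary time are also measured by accelerometer, and sitting has its own questionnaire.

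Four stronger readings are tempting, and the document does not support them:

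- *The score measures hours worked and not physical activity.* Six of the seven categories are active ones, and for women without sedentary employment the total is unaffected.
- *The variance doubles or quadruples.* That holds only at a single visit under assumed inputs. The planned baseline adjustment reduces it as shown in the working.
- *The treatment effect will have the wrong sign.* This needs desk hours to change differently between groups. The article gives no return-to-work or employment figures.
- *A desk job swamps the 3 h per week of training.* The instrument covers housework and employment. The supervised sessions fall under neither, so they are not the signal it would detect.

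**Conclusion.** The point holds in limited form. As written, sedentary employment hours count as physical activity in this total, which conflicts with the treatment of sitting in accelerometry, the Sedentary Behavior Questionnaire and the leisure instrument. For women with sedentary jobs, the total cannot register a one-for-one move from sitting to active work, and it follows changes in paid desk hours. Women with no sedentary employment at any assessment are unaffected.

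The size of the distortion is unknown, because the article gives no employment data. The loss of precision of about 9–13% assumes stable job hours, a between-visit correlation of 0.7 for active hours, and the assumed job shares and hours; at a correlation of 0.5 it is 17–25%. Bias in the group comparison arises only if desk hours change differently between groups, which can be neither shown nor excluded from the document.

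Materiality is low. This is one self-report measure in a secondary domain that also has objective measurement. The primary outcome and the sample size, which rests on the Fibromyalgia Impact Questionnaire, are untouched.

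**What to change.** Revise the scoring sentence so that:

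- the activity outcome is the sum of light, moderate and heavy hours, home plus employment;
- sedentary employment hours are reported separately, under sedentary behaviour;
- the all-category sum appears only as a supplement, labelled total home and work hours.

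The change takes a sentence or two. It needs no new data, because hours are already recorded by category. The downside is that the main total is no longer directly comparable with earlier reports that used the all-category sum; the supplement keeps that comparison available.
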